#### Step II

Accepting an alfa risk of 0.05 and a beta risk of 0.20 in a bilateral comparison between the study group and the control group, 312 individuals will be required (156 in each group) to detect differences in INR figures equal or higher than 15% between the groups for the primary target. It has been estimated by the researches that there will be a tracking loss rate of 10%. It will be assumed these lost individuals are impossible to locate or are those who do not wish to take part or cannot attend the scheduled revisions, in accordance with the study intervention plan, as well as deaths occurring within 6 months of the intervention. Given the relevant impact of the development of cardioembolic or hemorrhagic events due to out of range INR control values, changes of approximately 15% could have significant clinical relevance.

Patients will be recruited from the list of patients taking anticoagulant drugs included in the digital medical record according to the inclusion and exclusion criteria. The recruitment period will last for 1 month.

To reach the required sample size, all patients from the four health centers on AOT using vitamin K antagonists will be studied. Patients will be selected from their own PCC once identified by “Seguridad Social de Andalucia” user number (NUSSA). Once the inappropriate individuals are identified, they will be consecutively placed considering their social security number in every health center. After that, patients in each strate (PCC) will be randomly distributed in the intervention group or the control group. The investigators will try to avoid bias depending on each health center issues.

It has been estimated a follow-up loss ratio of approximately 10%. Deaths 6 months from the intervention, and inability to locate individuals, or not attending to the scheduled meetings will be considered as losses when dealing with the study intervention program.

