### Description of the intervention

The study will be carried out over a 28-month period. It started on 1 September 2018, and it will finish on 31 December 2020. Participants will be contacted by phone. Trial information with details will be explained to them, and they will be asked whether they are interested in taking part. At the same time, they will be scheduled for the group meetings. Signed informed consent forms will be obtained when the patient attends the health center before the group meetings begin. Patients in each strate (PCC) will be randomly distributed to the intervention group or the control group (a random numbers table will be used). The allocation sequence will be generated by the researcher team. The allocation concealment mechanism consists of organizing patients considering their Andalusian Health Service Number of Clinical Record (AHNCR). After assignment to an intervention, participant names will be deleted by the nurses in charge of the recruitment in order to mask the data. The outcome assessors will not know the patients’ identity. The masking will be carried out by replacing the patients’ identification data with an assignment number.

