### Timetable and work program

The study is being carried out over a 28-month period. The assembly of the project took place on 1 day at the Primary Care Center *Ciudad Jardin* practice classroom for all healthcare members involved in the research, along with the expert patient who will execute the intervention. The nurses will explain to the participants about the study approach, and they will collect the consent forms from the participants.

In the first step, at the start of the study, a retrospective data collection of the 6 months prior to the intervention will be completed from all patients who meet the selection requirements and are included in the AOT program. Once the anticoagulated patients have been analyzed and the list of the patients on inappropriate control has been completed, a random sampling will be done in every health center in order to build two groups: *intervention group and control group*.

The intervention group will include the indicated patients. Nurse students will take on the telephone calls to schedule intervention group patients for group meeting attendance. The main researcher and the expert patient will attend every group meeting, but the researcher will act just as an observer. Every participant center will rely on nurses (10 partners) and two resident medical interns (learning Family and Community Medicine) to complete this task. Due to their frequent contacts with anticoagulated patients, the nurses will instruct them about study issues and will collect the signed written consent forms; also, they will be involved in data collecting, INR figures, and patient study variables.

A portfolio with the collected data forms will be distributed to every participant. It will be employed by the patients to collect their data, which will be transcribed to a digital book. This book will be identical for every participant center and it will be used as a basis for the randomization. Two resident medical interns will handle all of the computerized recordings.

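### Ordering patients by record number is described as allocation concealment, but it hides no assignment, and the arm can be known before consent is signed

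*Protocol article*

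**What the plan says.** All references are to the protocol article.

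- *Description of the intervention*, on concealment: "The allocation concealment mechanism consists of organizing patients considering their Andalusian Health Service Number of Clinical Record (AHNCR".
- Same section, on who makes the sequence: "The allocation sequence will be generated by the researcher team".
- Same section, on the method: "Patients in each strate (PCC) will be randomly distributed to the intervention group or the control group (a random numbers table will be used".
- Same section, on identities: "After assignment to an intervention, participant names will be deleted by the nurses in charge of the recruitment". A number then replaces the identity so that outcome assessors are masked.
- Same section, on the order of events: one telephone call explains the trial, asks about interest and books the group meetings. Written consent is taken later, at the health centre, before the meetings start. Control patients attend none of the sessions.
- *Step II*: once poorly controlled patients are identified, "they will be consecutively placed considering their social security number in every health center", and they are then randomised within centre.
- *Timetable and work program*: when the list of poorly controlled patients is complete, "a random sampling will be done in every health center in order to build two groups". Of a digital book of transcribed patient data it says: "it will be used as a basis for the randomization".

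**The concern.** Allocation concealment means that whoever decides on a patient's entry, and the patient, cannot know the arm until entry is settled. The article addresses concealment directly and names a step that does something else. A sorted list tells everyone who is where; it keeps nothing from anyone.

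The staff concerned know a good deal about each patient. The list consists of people whose INR control has just been assessed, and the nurses who explain the study also collect consent and INR data. If the arm is known while consent is still open, two things can happen. Staff may press harder for some patients than for others, and patients offered an evening session may accept or decline for reasons that do not apply to usual care. Either would make the enrolled groups differ in motivation or likely adherence, and both plausibly affect time in therapeutic range, the primary outcome. The planned intention-to-treat analysis keeps enrolled patients in their assigned arm, but it does not restore people who never enrolled because they knew the arm.

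**Working it through.** The plan gives no figure on this point, so the check sets its statements side by side.

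**Step 1. Does any stated element hide the assignment from those who enrol?**

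| Stated element | What it achieves | Hides the arm before entry? |
|---|---|---|
| Ordering by AHNCR | Fixes position on the list | No |
| Random numbers table within centre | Generates the assignment by chance | No; this is generation |
| Sequence made by the research team | Says who generates it | No; nobody independent of recruitment is named |
| Names deleted and replaced by a number | Masks outcome assessors | No; it happens after assignment |

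None does. The last row matters because it could be mistaken for concealment. It protects outcome assessment, and it also shows that recruiting nurses hold named records when the arm already exists.

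**Step 2. When can the arm become known relative to consent?**

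1. Group meetings are booked in the first call (*Description of the intervention*).
2. Only the intervention arm attends them (same section).
3. Booking a meeting for the right people therefore presupposes the arm, unless everyone is booked provisionally, which is not stated.
4. Signed consent comes after that call (same section; the next paragraph places it at INR control appointments).
5. *Timetable and work program* fits this order: the two groups are built from the completed list, and calls are then made to schedule intervention patients.

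Written consent is also an inclusion criterion, which would point to consent before randomisation. The article never states that order, and points 1 to 5 allow the reverse.

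**Step 3. Does the plan foresee refusals at this stage?** Yes. *Step II* counts among the expected losses (about 10%) people who do not wish to take part or cannot attend. The plan thus expects some listed patients to decline, and nothing requires that they decide without knowing the arm.

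**Step 4. Is the list order defined once?** *Step II* orders by social security number and *Description of the intervention* by AHNCR. These may be one identifier under two names, but the article does not say so. A procedure that reads a random numbers table against a list can be reproduced only if the list order is fixed, so the two sections must be reconciled.

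**The case against.** The best defence has three parts.

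*Allocation is done in one batch.* Groups are built after the list is complete, so no recruiter can guess the next assignment and hold a patient back. Ordering by an arbitrary, pre-existing number also limits discretion over who sits where. This stands as far as it goes: it reduces the scope for steering generation. It does not reach the consent stage, where the arm may already be known.

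*An article condenses.* Who holds the sequence and how the table is read are details commonly left to the full protocol. That is fair for those details, and their absence is not held against the plan. The concealment sentence is different: it states what the mechanism consists of, and that statement is wrong.

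*The two numbers may be the same.* This is possible, and it is why the identifier point is a request to reconcile and no more.

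Stronger readings are tempting, and the document does not support them.

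- A reader might count three ordering bases by adding the digital book. The article calls the book a basis for randomisation, which is a data source, not an ordering key. Only two keys are named.
- A reader might infer unrestricted randomisation, with unequal arms or more intervention patients than session places. No sentence says so. Random sampling to form two groups of 156 is compatible with drawing half of each centre's list, and 156 fits within the 11 × 15 = 165 places. Even under simple randomisation of 312, the 95% range for one arm is 156 ± 1.96 × √78, or 139 to 173. With the effect that gives 80% power at 156:156, power at 139:173 is Φ(2.80 × √(4 × 139 × 173 / 312²) − 1.96) = Φ(0.82), about 79.5%. Imbalance of that kind is chance, not bias.
- A reader might infer that the team can choose the starting point in the table or repeat the draw. The article is silent on this, so it is conjecture.

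**Conclusion.** The point holds in this form: the stated concealment mechanism is not one, and the stated order of telephone booking, assignment and consent lets the arm be known before enrolment is complete. Selection bias is therefore possible under the text as written. Its size cannot be given, because the document has no data on refusal by arm or on how far refusal relates to INR control. The conclusion rests on reading the meeting booking in the first call as arm-specific. If every patient was booked provisionally and arms were released only after signature, the exposure largely disappears, but the article would need to say so, and the concealment sentence would still be wrong. Nothing here shows that allocation was not random or that bias occurred. The differing names for the ordering number are a secondary inconsistency. The point deserves correction because the analysis cannot repair selection at entry and the remedy is cheap.

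**What to change.** Replace the concealment sentence with a procedure along these lines:

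1. Each centre's list of patients who have signed consent is frozen under one named identifier, used alike in *Step II* and *Description of the intervention*.
2. The list goes, as study codes without INR history, to an existing team member who has no patient contact.
3. That person allocates half of each centre's list with a seeded script in R, the software already named under *Statistical analysis*. Seed, script and output are archived.
4. Arms are released to the centres only from that output and only after consent. Meetings are booked after release.

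This needs some protocol text, a short script and a modest change of sequence: consent has to be collected before meetings are scheduled, which may lengthen the one-month recruitment period slightly. It needs no additional patients, staff or software.

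The study started on 1 September 2018, so allocation may already be complete. In that case, report how it was done: who made the sequence, which number ordered the lists, and whether consent came before or after the arm was known. Withdraw the claim that ordering concealed the allocation.

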#### Data collection

Plans to collect variables will consist of an analysis of the digital medical records in order to obtain the patients’ clinical information. Meetings have been carried before the beginning of the research among the researchers to unify data collecting criteria. Data collecting forms are available as attached documents to this protocol. All of the variables detailed below will be collected as long as they are suitably listed in the digital medical history or could be directly obtained from the patient during the medical interview, without the need for changing the health center’s usual clinical practice, over the 6 months prior to the intervention. Any data required to support the protocol can be supplied on request. The data will be collected on the collection sheets and kept by the principal investigator as follows.

#### First step

Patients on AOT programs will be enrolled from several primary health centers from a healthcare area of Málaga. They will be evaluated on their clinical characteristics. The measurements obtained from the digital clinical history over the last 6 months before the beginning of the study will be recorded, as well as the rest of the variables, in the collection sheets.

#### Second step

Once the study of the VKA anticoagulation control degree is performed, patients who present inappropriate control values will be selected. A list of patients with deficient INR control at the participant health centers will be made. An inappropriate INR control is defined as when the therapeutic INR values (range from 2 to 3, or to 3.5 in prosthetic valve wearers) percentages (TRT) are less than 65%, using the Rosendaal method to obtain them. In cases of no availability, INR controls will be considered inappropriate when the therapeutic INR value percentage results are less than 60% of the total measures. For any of the assumptions, the assessment period is at least the last 6 months. There is no anticipated harm and compensation for trial participation. As a provision for post-trial care, patients on inappropriate INR control figures will be indicated to stop vitamin K antagonist intake. They will be indicated to start a non-vitamin K antagonist oral anticoagulant (NOAC) intake if they suffer from atrial fibrillation and anticoagulation criteria exist.

The data monitoring committee is composed of the main researcher ([name]) and doctors [name] and [name]. This committee is independent of the sponsor, and funding is not made under any term.

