### Inclusion and exclusion criteria

#### Inclusion criteria

Men and women over 18 years old affiliated to one of the 4 primary care centers selectedPatients on VKA treatment for at least the last 6 months in a primary care environmentPatients showing INR level control values under 2 or above 3 (out of range)Patients for whom we have access to, at least, 80% of their INR level controls in the last 6 months of treatment with VKA, even though they are enrolled in another primary care centerPatients who give written informed consent to take part in the study

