#### Step I

Considering that the prevalence of patients on AOT is about 1.5% of the general population, it can be claimed that the target population to initiate our study will be 750 anticoagulated patients (using anticoagulant drug consumption data from our health área in Málaga, Spain). Prior studies indicated [15–17] that at least 33% of these patients would not have an appropriate INR control level (INR values above 2 and under 3 or under 3.5 for prosthetic valve wearers). To reach an appropriate sample size in the estimated proportion, the following terms must be considered: (1) using a normal asymptotic confidence interval with a correction to finite populations on bilaterally of 95%, (2) assuming that the expected population is approximately 33%, and (3) since the population total size is 750, it was deemed necessary to include 312 experimental units in this study (Fig. 1).

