### Variables: operative definition

The main variable to be assessed in this study is time on INR therapeutic levels in the last 6 months of receiving VKA treatment. Appropriate INR level control will be assessed in two ways: measuring the therapeutic INR value percentages or time percentages in therapeutic values estimated using the Rosendaal method. It records the figure percentages as defined by their acceptable values according to the pathology the patient suffers from. This is from 2 to 3 for atrial fibrillation or from 2.5 to 3.5 if thromboembolism prevention is carried out after a heart valve surgery has been performed. Therefore, this quantitative variable had to be measured to calculate the patient’s percentage of an appropriate range, according to the patient’s condition.

Independent variables, also called study variables, are those that could affect the result variables. We classified them into eight groups to make their analysis easier.

Sociodemographic: age and sex, marital status, employment situation, and social and family support.

Somatometry and vital signs: height, weight, body mass index (BMI), diastolic and systolic blood pressure, and heart rate.

Cardiovascular risk factors: smoking habit, diabetes, arterial hypertension, dyslipidemia, and chronic renal failure.

Cardiovascular conditions: atrial fibrillation (AF), interventional cardiac valve diseases with or without AF, ischemic cardiopathy, thromboembolic disease history (stroke, transient ischemic attack), hemorrhagic stroke, and congestive heart failure.

Blood test: complete blood count, bleeding time and prothrombin time or partial thromboplastin time, glomerular filtration rates, total cholesterol, HDL and LDL cholesterol, and triglycerides. They were obtained from the last blood test carried out for the patient.

Use of accompanying medication: total number of drugs and anticoagulant type.

Consumption of “gastric protector” or nonsteroidal anti-inflammatories.

Dietary habits: usual consumption of food rich in vitamin K, alcohol consumption, and frequent diet transgressions.

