### Secondary outcome measures

2.Sociodemographic: record of age and sex [time frame, start of the study]3.Body mass index (BMI): determination of the body mass index calculated as the weight measured in kilograms (kg) divided by the height measured in meters squared (weight/height^2^) (kg/m^2^) [time frame, 0 and 6 months]4.Diastolic and systolic blood pressure: determination of diastolic and systolic blood pressure measured in millimeters of mercury (mm/Hg), average of 2 determinations [time frame, 0 and 6 months]5.Heart rate: determination of the number of heartbeats per minute, average of 2 determinations [time frame, 0 and 6 months]6.Smoking habit: incidence of smoker’s habit status in the electronic medical record [time frame, 0 and 6 months]7.Diabetes: incidence of the condition of diabetes in the electronic medical record [time frame, 0 and 6 months]8.Arterial hypertension: incidence of the diagnosis of hypertension in the electronic medical record [time frame, 0 and 6 months]9.Dyslipidemia: incidence of the diagnosis of dyslipidemia in the electronic medical record [time frame, 0 and 6 months]10.Chronic renal failure: incidence of the diagnosis of chronic renal failure in the electronic medical record [time frame, 0 and 6 months]11.Atrial fibrillation: incidence of the diagnosis of atrial fibrillation in the electronic medical record [time frame, 0 and 6 months]12.Interventional cardiac valve diseases with or without atrial fibrillation: incidence of the diagnosis of interventional cardiac valve diseases in the electronic medical record [time frame, 0 and 6 months]13.Ischemic cardiopathy: incidence of the diagnosis of ischemic cardiopathy in the electronic medical record [time frame, 0 and 6 months]14.Thromboembolic disease history (stroke, transient ischemic attack): incidence of a thromboembolic disease history (stroke, transient ischemic attack) in the electronic medical record [time frame, 0 and 6 months]15.Hemorrhagic stroke: incidence of the diagnosis of hemorrhagic stroke in the electronic medical records [time frame, 0 and 6 months]16.Congestive heart failure: incidence of the diagnosis of congestive heart failure in the electronic medical records [time frame, 0 and 6 months]17.Glomerular filtration rates: determination of the total glomerular filtration rates in ml/min/1.73 m^2^; change from basal to 12 months [time frame, 0 and 6 months]18.Total cholesterol: determination of total cholesterol measured in milligrams per deciliter (mg/dl); change from basal to 12 months [time frame, − 6 and 6 months]19.HDL cholesterol: determination of high-density lipoprotein cholesterol (HDLc); LDLc measured in milligrams per deciliter (mg/dl) (low-density lipoprotein cholesterol); HDLc measured in milligrams per deciliter (mg/dl); change from basal to 6 months [time frame, − 6 and 6 months]20.LDL cholesterol: determination of low-density lipoprotein cholesterol (LDLc); LDLc measured in milligrams per deciliter (mg/dl); change from basal to 6 months [time frame − 6 and 6 months]21.Triglycerides: determination of total triglycerides measured in milligrams per deciliter (mg/dl); change from basal to 12 months [time frame, − 6 and 6 months]22.Total number of drugs: determination of the total number of different medications prescribed in the electronic medical records; change from basal to 12 months [time frame, − 6 and 6 months]23.Anticoagulant type: determination of the anticoagulant type prescribed in the electronic medical records; change at baseline and at 12 months [time frame, − 6 and 6 months]24.Consumption of “gastric protector”: determination of the consumption of “gastric protector” prescribed in the electronic medical records; change at baseline and at 12 months [time frame − 6 and 6 months]25.Usual consumption of food rich in vitamin K: change in usual consumption of food rich in vitamin K; change at baseline at 12 months [time frame, − 6 and 6 months]26.Alcohol consumption: change in usual alcohol consumption; change at baseline and at 12 months [time frame, − 6 and 6 months]27.Eligibility: minimum age, 18 years; sex, all; accepts healthy volunteers, no

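### The post-trial rule stops the vitamin K antagonist in every poorly controlled patient but names a replacement only for those with atrial fibrillation, although valve patients without it are eligible

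*Protocol article*

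**What the plan says.** The rule on care after the trial is in the Second step section of the protocol article and consists of two sentences. The first reads "As a provision for post-trial care, patients on inappropriate INR control figures will be indicated to stop vitamin K antagonist intake". The second has these patients start a NOAC "if they suffer from atrial fibrillation and anticoagulation criteria exist".

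The same section defines inappropriate control shortly before this rule, and that definition gives one patient group its own upper INR limit: the range runs from 2 to 3, "or to 3.5 in prosthetic valve wearers". Step I does likewise ("under 3.5 for prosthetic valve wearers"). Variables: operative definition sets a target range "from 2.5 to 3.5 if thromboembolism prevention is carried out after a heart valve surgery has been performed".

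The recorded conditions include "interventional cardiac valve diseases with or without AF", and the list of secondary outcome measures repeats this ("Interventional cardiac valve diseases with or without atrial fibrillation").

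On indication, the inclusion criteria ask only that patients be "on VKA treatment for at least the last 6 months in a primary care" setting. The exclusion criteria cover cognitive impairment, limited mobility, terminal illness, addiction, severe psychiatric illness and inability to attend. None of them refers to the reason for anticoagulation.

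**The concern.** The two sentences cover different sets of patients. Stopping depends on INR control alone. Starting a replacement depends on INR control and also on atrial fibrillation with criteria for anticoagulation. Anyone in the first set but not the second is told to stop one anticoagulant and is given no other.

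This is a matter of patient safety. The Background section names deep vein thrombosis, pulmonary embolism and prosthetic heart valves, alongside atrial fibrillation, as the main indications for oral anticoagulation. A rule that, followed as written, withdraws treatment from patients with the first three conflicts with the article's own rationale. The rule could also be triggered often: every participant is selected for poor control, and the control arm receives usual care only, so some participants may well still meet the definition at 6 months.

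The provision applies after the trial, so no bias in the 6-month comparison is claimed.

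**Working it through.** No planned figure needs reproducing; the check is a comparison of the article's own statements.

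**1. Who is told to stop.** Second step, first sentence: patients with inappropriate INR control. There is no condition on indication.

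**2. Who is told to start something else.** Second step, second sentence: those of the same patients who have atrial fibrillation and meet criteria for anticoagulation. By its grammar, the condition governs starting the NOAC and not stopping the vitamin K antagonist.

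**3. Whether anyone falls between the two.**

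| Question | Where | Answer |
|---|---|---|
| Is atrial fibrillation required for entry? | Inclusion criteria | No; at least 6 months of vitamin K antagonist treatment is enough |
| Is any indication excluded? | Exclusion criteria | No |
| Are prosthetic valve wearers expected? | Step I; Second step; Variables: operative definition | Yes; they have their own INR limits |
| Are valve patients without atrial fibrillation expected? | Variables: operative definition; Secondary outcome measures | Yes; recorded with or without it |
| Are other indications acknowledged? | Background and current status | Yes; deep vein thrombosis and pulmonary embolism |

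A valve patient without atrial fibrillation whose control remains poor therefore meets the stop sentence and fails the start sentence. The definition of inappropriate control that triggers the rule names prosthetic valve wearers explicitly.

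**4. Whether another section closes the gap.** None does. No section gives patients without atrial fibrillation a replacement drug, an exception to stopping, or a referral. The Background lists heparin and the other anticoagulant classes as general options but assigns none to these patients. The statements that health professionals guide INR control (Description of the intervention) and that the research follows usual practice (Risks or limitations and viability) describe conduct during the study.

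**5. Illustration of size.** The article gives neither the share of participants without atrial fibrillation nor the share still poorly controlled at 6 months. Both are assumed here: 5% to 30% for the first, and 50% to 100% of those for the second. The total of 312 is from Step II.

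Number affected = 312 × share without atrial fibrillation × share of those still poorly controlled

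- Low end: 312 × 0.05 × 0.50 = 7.8, about 8
- High end: 312 × 0.30 × 1.00 = 93.6, about 94

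These figures make no allowance for the 10% loss that Step II expects. With it, 312 × 0.90 = 280.8 remain, and the range becomes 280.8 × 0.05 × 0.50 = 7.0 to 280.8 × 0.30 × 1.00 = 84.2.

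**The case against.** The strongest reply is that the two sentences form one instruction. The second follows at once and refers to the same patients, so the pair can be read as: where atrial fibrillation and the criteria are present, replace the vitamin K antagonist with a NOAC. The English of the article is loose in places, so the position of a condition is weak evidence of intent. That reading is plausible and may well be what was meant. It does not settle the matter, because the text does not say it and a safety instruction should not need a favourable reading.

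A second reply is that not naming a replacement is different from ruling one out, and that treating clinicians would decide. It is true that the article nowhere says these patients must go without anticoagulation, and a clinician might well not follow the rule literally. But the sentences cited for clinician control concern the study period, and they do not limit the stop sentence.

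A third reply is that a journal article condenses the full protocol, which may set out switching by indication. That would answer a complaint about missing detail. Here the article states a rule, and the rule as stated is wrong for eligible patients.

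The objection to the numerical range is largely right. Both shares are assumed, the top end is extreme, and the range ignores participants who are lost or who stop the drug during the study. It serves only as an illustration. It is also correct that nothing in the trial's inference is touched.

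**Conclusion.** The concern holds. The stop instruction is unconditional, the replacement is restricted to atrial fibrillation, and the article's own eligibility criteria, INR ranges and recorded conditions show that patients outside that restriction can be in the trial. Prosthetic valve wearers without atrial fibrillation are the clearest case; patients treated for venous thromboembolism are another.

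The conclusion rests on the wording as printed and makes no assumption about intent. Its size cannot be established from the article: the illustrative 8 to 94 of 312 depends wholly on assumed shares, and a single affected valve patient would justify the correction. Sample size, procedures and the 6-month analysis are unaffected. The change should be made, but it does not threaten the primary result.

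**What to change.** Replace the two sentences in Second step so that one condition governs both stopping and switching, and so that everyone else has a stated path. For example:

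> After the trial, patients with atrial fibrillation whose INR control is still inappropriate and who meet the criteria for a NOAC will be advised to change from the vitamin K antagonist to a NOAC. All other patients with inappropriate control, including prosthetic valve wearers, do not stop the vitamin K antagonist under this provision; they continue it or are referred to the treating clinician for individual review.

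The second sentence prescribes no drug for the other indications. It removes the automatic stop and leaves the choice to the clinician.

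The cost is a two-sentence wording change, reported to the ethics committee by the amendment route the article already describes. Sample size, trial procedures and analysis stay as they are.
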